## Abstract

Shinrin-yoku, forest bathing, may provide relief from chronic and breakthrough pain in patients with axial spondyloarthritis and improve immune function through increasing NK cell numbers and activity and their downstream effectors, perforin and granulysin, after chemo- or radiation therapy in breast and prostate cancer patients. The aim of this paper is to describe the study protocol for a simulated forest immersion therapy using virtual reality and atomized phytoncides, volatile organic compounds found in forested areas designed to effect positive change for these two patient populations. The setting, including the room set up and samples with inclusion/exclusion specific to this type of intervention, is outlined. Measures and calibration procedures pertinent to determining the feasibility of simulated forest immersion therapy are presented and include: ambient and surface room temperatures and relative humidity in real time, ambient ultrafine particulate matter, ambient droplet measurement that coincides with volatile organic compounds, specific phytoncides, and virtual reality and atomization of phytoncide set up. Particular lessons learned while training and setting up the equipment are presented. Simulated forest immersion therapy is possible with attention to detail during this early phase when development of methods, equipment testing, and feasibility in deploying the intervention become operational. The expected outcome of the development of the methods for this study is the creation of a standardized approach to simulating forest therapy in a controlled laboratory space.

## 1. Introduction

Shinrin-yoku, roughly translated as forest bathing, is the traditional Japanese practice of immersing oneself in nature by mindfully using our senses, such as sight and smell [1,2]. Shinrin-yoku practices range from sitting quietly and enjoying the forest to walking or hiking through forested areas [3]. The key to shinrin-yoku is connecting with the atmosphere of the forest, taking in forest aerosols, volatile organic compounds known phytoncides [4]. Phytoncides are inhaled airborne particles that trees naturally emit during different stages of development [5,6,7,8,9].

In 1982, the Japanese Ministry of Agriculture, Forestry and Fisheries began researching the health benefits of shinrin-yoku [2]. There are several therapeutic effects of shinrin-yoku in the context of depression, including improving immune system function, such as decreased pro-inflammatory cytokine activity and increased in anti-inflammatory cells, decreased depressive symptoms, stress, and anxiety, improved mental relaxation and attentional focus, and increased feelings of awe, gratitude, and selflessness [4,9,10,11,12,13,14,15,16]. The benefit of forested greenspaces for human psychology and physiology is a reduction in stress [14,17], which in turn positively impacts mood [18] and further reduces inflammation [19]. In the context of normal male subjects, after both shinrin-yoku forest immersion and hotel/sleep-based phytoncide humidification with α-pinene, β-pinene, and d-limonene, the following immune system improvements were found: natural killer T-cell numbers and activity increased, as did perforin and granulysin [6,20,21].

In 2017, a research agenda for nature contact and health was published with several research domains, including the mechanistic biomedical studies domain (1.0) for future research development [17]. We developed a simulated forest immersion therapy (SFIT) that includes both forest aerosols and virtual reality based on this research agenda. We are interested in psychological and physiological variables that suit our differing populations of interest (i.e., axial spondyloarthritis patients with chronic or breakthrough pain or breast and prostate cancer patients who have undergone chemo- or radiation therapy and have NK cell depletion), and these align with the mechanistic biomedical domain [17]. Specifically, our research objectives are to elucidate 1.1: to what extent stress reduction mediates observed health benefits of nature contact; 1.1b: which natural elements are most associated with stress reduction; 1.2: to what extent improved immune function mediates observed health benefits of nature contact; 1.2b which natural elements are most associated with improved immune function; and 1.2c which markers of immune function are the most useful for studying this effect [17]. If there are health effects of forest immersion, then could the same health benefits be achieved with simulated forest immersion as a way of providing therapy to patients not able to exercise or move in outdoor forests or greenspaces due to debility or frailty from chronic illness (i.e., chronic and breakthrough pain) or acute illness (i.e., recovery of immune system function after chemo- or radiation therapy in cancer)?

### 1.1. Significance

An estimated 1,806,590 new cases of cancer will be diagnosed in the United States each year, of which 281,550 will be breast cancer and an estimated 248,530 will be prostate cancer [22]. Additionally, up to 1% of the population of the United States, an estimated 2.7 million people, may have axial spondyloarthritis [23], and 50% of them suffer from chronic widespread pain [24,25] and breakthrough pain after standard treatment in approximately 60% of people [26]. Using complementary interventions to improve outcomes in patients who are seriously ill is paramount to extending healthcare to vulnerable populations. We hope to accelerate the translation of findings for healthy individuals for the implementation of a novel minimally invasive immune therapy for cancer patients with solid tumors where NK cells are depleted, both in number and activity [27,28], and to determine clinically meaningful protocols for the management of pain, and comorbid symptoms of pain, in patients with axial spondyloarthritis with chronic and breakthrough pain.

Forest bathing, virtual reality (VR), the use of phytoncides, and their separate or combined effects constitute a new research avenue. It is intriguing to explore the effects of nature-based interventions on chronic and breakthrough pain in patients with axial spondyloarthritis, as well as the effects on the immune system, and how we might harness them to benefit acutely ill patients who are immunocompromised.

### 1.2. Background

#### 1.2.1. Psychological Pathways of Interest

Contemporary theories, such as Kaplan’s Attention Restoration Theory [29,30], Ulrich’s Stress Reduction Theory [31,32,33], and Kellert and Wilson’s Biophilia Hypothesis [34,35] provide a conceptual framework for the practice of shinrin-yoku and engaging with nature in various forms of nature therapy. Shinrin-yoku researchers Song, Ikei, and Miyazaki (2016) developed a conceptual framework based on an extensive review that describes how the restorative effects of nature increase physiologic immune system recovery from stress as well as physiologic relaxation [36].

Kaplan and Kaplan hypothesized that exposure to natural settings through the five senses has a direct effect on parasympathetic nervous system activation, thus leading to states of greater awareness achieved through relaxation [29]. Ulrich’s Stress Reduction Theory [31] was developed from observational studies wherein patients in hospitals with patient room windows facing nature-laden scenery (e.g., trees, green foliage) experienced marked improvement in health and recovery with shortened hospital stays compared to patients in rooms with an urban view [31,32]. Wilson’s Biophilia Hypothesis [35], suggests that humans have a developmental affinity for natural surroundings, and being immersed in nature is therefore innately appealing. This research suggests that a disconnect from nature has adverse health impacts [34], and therefore finding effective means for individuals to access nature is crucial [37,38].

#### 1.2.2. Pain

Pain reduction is an emerging field of study in greenspace interventions [39], particularly the relationships between pain, stress, and the burden of chronic illness [40,41,42,43,44]. To date, several studies describe the pain-reducing effects of viewing nature (e.g., simulated greenspaces) in clinical settings for acute and chronic pain populations [37,41,45,46,47,48,49].

Simulated nature and greenspace exposure has been applied in clinical settings for the treatment of acute [41,46,47] and chronic pain [37,44,50]. Virtual reality (VR)-based therapies for pain reduction are not new, and several theories for how and why VR-based therapies improve pain outcomes center on the element of “distraction”, such that the virtual viewing experiencing distracts an individual from feeling their pain [51,52,53,54]. This is largely based on the Gate Control Theory proposed by Melzack and Wall [55], which suggests that the attention paid to the pain experience, as well as the emotion tied to the experience of pain, which includes past emotional memories, play a role in pain interpretation; therefore, directing attention away from the experience of pain may reduce the sensation of pain [47,53,56,57,58,59].

Research on VR-based greenspaces or nature exposure for pain reduction describes VR as a tool for delivering nature, and that nature is the crucial element within the interventional design [47]. In a repeated-measures design, 50 patients attending chemotherapy sessions were evaluated for pain and stress during intravenous port access. While findings were insignificant after one nature-based VR session, participants reported feeling relaxed, peaceful, and distracted by positive thoughts [47]. Potential benefits of virtual nature directly link to the theories describing the health effects of shinrin-yoku, including improved relaxation, restoration, and alertness, improved functioning of the immune system, and reduced exposure to air pollution and urbanicity [37]. Exposure to greenspaces can induce relaxation via psychoendocrine pathways, including the function of the hypothalamic–pituitary–adrenal (HPA) axis and resulting cortisol secretion [60,61]. Further, exposure to greenspaces, which include greenery in the form of foliage, trees, and vistas, such as with shinrin-yoku, improves health outcomes whether the exposure involves “live” nature or virtual nature [62,63].

#### 1.2.3. Biological Pathways of Interest

Immune suppression is a major issue for adults with a cancer diagnosis receiving chemo- and/or radiation therapy. In particular, NK cell suppression in this population is problematic as NK cells are the major immune cell type surveilling foreign or infectious antigens and eliminating them [64]. Thus, implementation of a novel minimally invasive immune therapy in cancer patients with solid tumors where NK cells are depleted, both in number and activity, is crucial [27,28]. Patients with solid tumors that have activated NK cells within the tumor have longer overall survival [65,66]. Blood levels of NK cells are essential to the movement of NK cells into tumor tissue.

Research shows positive effects of forest bathing on NK cell numbers and activity [67] (NK CD3^−^/CD56^+^/ and NK CD3^−^/CD56^+^/CD69^+^, respectively) and on expressed proteins, such as perforin and granulysin [6,20,68,69]. NK cells use pattern recognition molecules (epitope) on the surface of transformed or stressed cells to accelerate detection and elimination of problematic cells. Perforin and granulysin are key to enabling the natural killing mechanism of the NK cell [70]. Perforin is a downstream effector related to the number and activity of the NK cells [64]. Perforin creates a pore in the target cell once the target cell’s epitope is recognized [64]. The pore allows granulysin to enter the cell and effect apoptosis of the intracellular structures; the cell lyses and dies [5,64]. Perforin and granulysin are needed to maintain normal immune surveillance and reduction in infection, specifically in immunocompromised cancer patients [27,28].

Two proof-of-principle studies were conducted in middle-to-older-aged healthy men. These two studies, a 3-day forest experience (immersion experience) and a 3-night hotel experience, measured or used humidified-forest-derived volatile organic compounds, known as phytoncides, respectively. Of the phytoncides tested, humidified α- and β-pinene and limonene in combination produced an increased number of NK cells and elevated activity [6,20].

### 1.3. Purpose

If forest immersion can provide immune system benefits in healthy men (i.e., improved NK cell numbers and activity, increased perforin and granulysin), can dispersal of three phytoncides (α- and β-pinene and limonene in combination) paired with a greenspace virtual reality provide the same positive effects on NK cells in patients with solid tumor cancer who have completed cancer therapy? Additionally, can humidified limonene paired with virtual reality reduce pain and psychological stress in patients with axial spondyloarthritis? Our purpose is to deploy a standardized study protocol for simulated forest immersion intervention in cancer patients with NK cell depletion and patients with axial spondyloarthritis with chronic and breakthrough pain to test its feasibility and rigor. The simulated forest immersion intervention will provide greenspace/forest experience through three of the five senses. Virtual reality will provide visual and auditory stimuli. Humidified aromatic forest oils will provide olfactory stimuli. Virtual reality and atomized forest oils may be used in combination or alone [71]. Two distinct studies will use this standardized protocol for (1) cancer patients and (2) patients with axial spondyloarthritis. The purpose of this paper is to outline the development of the study protocol for the intervention and the control conditions of the clinical lab setting.

## 2. Methods/Approach

### 2.1. Research Design

We will use a two-arm study design with concurrent controls selected from the breast and prostate cancer clinics and from the arthritis clinic with two measurement time periods to test the proposed simulated forest exposure intervention. In the SFIT study with patients with axial spondyloarthritis who have chronic or breakthrough pain, the two-time points were before and immediately after the intervention. In the SFIT study with patients with either breast or prostate cancer, the two time periods were before and on Day 3 after the intervention.

### 2.2. Study Sample

The study sample for study #1 will be recruited from cancer patients with solid tumors (HR + HER2- breast, or prostate cancer) who have completed cancer therapy (hormone therapy excepted) as this population may benefit the most from increases in NK cell number and activity, perforin, and granulysin to prevent infection as patients become relatively immunocompromised after chemo- or radiation therapy. For study #2, the study sample will be recruited from axial spondyloarthritis patients who have chronic or breakthrough pain, as virtual reality has been shown to reduce pain, and d-limonene administration in animals has shown pain reduction. Since the two studies are set in the future and are pilot studies, we expect for study #1 to recruit and enroll 25 participants and for study #2 to recruit and enroll 25 participants. For study #1, the participant number is limited by budget and the cost of pre-clinical and clinical laboratory tests. For study #2, the participant number is limited by budget and the cost of paper-based tools. Concurrent controls for both studies will be identified by the clinicians in either the cancer clinics or the arthritis clinic. Concurrent controls will meet the same study inclusion and exclusion criteria as those who are enrolled in the study interventions. We expect to have 4 of each of the assigned genders in the control groups. The control groups will be randomized to receive neither SFIT intervention, VR, or atomized phytoncides. They will be exposed to atomized water dispersal for 1 h, the same length of time as the study participants who will receive the SFIT interventions. All the same data will be collected for both study #1 and study #2 on these control participants. At the end of the studies, should an effect of the SFIT intervention be noted, the control participants will have the opportunity to complete the same intervention. Clinicians will lead the recruitment of these patients, followed by a phone screening for inclusion and exclusion conducted by the principal investigator and research associate.

#### 2.2.1. Inclusion and Exclusion for SFIT—General Considerations

Since we will be using atomized phytoncides as well as virtual reality, either in combination or separately, several exclusion criteria apply, as seen in Table 1.

##### Inclusion and Exclusion for SFIT for Breast and Prostate Patients

Participants will be included if they are willing and able to provide informed consent, are of either biological sex, older than 18 years of age, and have completed cancer therapy for HR + HER2 breast cancer or prostate cancer, Stage I–III, with no evidence of metastasis. Participants will be excluded if they have a history of autoimmune disease, are on immune modulating therapies (endocrine therapy allowed), have had surgery or an invasive procedure in the past two months, and recent infection in the past two weeks (these are known confounding variables in immune system measures of interest).

##### Inclusion and Exclusion for SFIT for Axial Spondyloarthritis Patients

Participants diagnosed with axial spondyloarthritis (axSpA) will be included if they are willing and able to provide informed consent and are at least 18 years of age or older, and they may be any sex or gender. Additional inclusion criteria are: a score of 4 or higher on the 10-point Bath Ankylosing Spondylosis Disease Activity Index (BASDAI) (a standard criterion for suboptimal control of symptoms and disease [78] with a correlation between patient-reported BASDAI scores and measurable disease) [79], and a rheumatologist overseeing their care. Participants will be excluded if they are in an active phase of treatment with biologic cytokine inhibitors (which may confound the effects of the intervention on outcomes measures) [80]. Use of commonly prescribed painkillers is acceptable, and we will control for their use in the analysis.

### 2.3. Setting

The SFIT Lab is located in our Integrated Bio-Behavioral Lab space within our school. The lab room, where the instrumentation for the SFIT is set up, is 20 feet × 15 feet with a 12-foot ceiling. The room has temperature control, so a consistent temperature between deployments of SFIT with participants can be maintained, as well as lighting control, so the lights can be dimmed when patients are using VR.

### 2.4. Intervention—Procedure

Our two studies are novel as no one to date has used simulated forest immersion in patients with acute or chronic morbid conditions. The principal investigator (PI) and research associate (RA) will implement SFIT in a separate room from the room used to cross-check inclusion and exclusion, obtain informed consent, collect baseline measures, and allow the participant to rest. Prior to the arrival of the participant, the SFIT intervention space will be prepared. Preparation of the intervention space includes calibration of the instruments that will measure volatile organic compound particles (phytoncides are volatile organic compounds) and droplets, room temperature and humidity, and room surface temperatures, followed by measurement of the ambient particles and droplets and room temperature and humidity prior to the implementation of the atomized phytoncides [71,81]. Phytoncides α-pinene, β-pinene, and d-limonene (Floraplex Terpenes, Ypsilanti, MI, USA) will be prepared for atomization with a commercially available atomizer (Asakuki 500 mL Premium Atomizer, Tronhon Co., Ltd., Chongqing, China) that can emit phytoncides for up to 3 h. Once the dose expected (0.80 ppm) reaches the dose published by Li [6], the participant will be brought into the intervention room. To date, the Li study, which was conducted with healthy men, has been the only study to record phytoncide dose in a controlled setting. We will use this concentration as the target dose for our humidified phytoncide set up. Both at the beginning and at the end of 1 h of exposure to the simulated forest immersion therapy intervention, ambient phytoncide in the contained space will be measured indirectly by measuring both the increase in ambient air particle mass and number, as well as by measuring the change in total volatile organic compounds (VOCs). Total particle numbers will be measured with a continuous ultrafine particle counter (P-Trak 8525, TSI, Shoreview, MN, USA), and the total VOCs will be measured with the portable handheld monitor (Mini ppbRAE 3000, Honeywell International INC.; San Jose, CA, USA). The P-Trak and Mini ppbRAE 3000 will measure the increase in particle numbers and water droplets (aerosol), respectively, which will serve as a surrogate of relative exposure to phytoncide. Continuous monitoring of room temperature and relative humidity will be measured by the HOBO MX2301 Temperature/RH Data Logger (ONSET, Bourne, MA, USA). Room surface temperature will be measured by ADC Adtemp Mini 432 Non-Contact Infrared Thermometer (American Diagnostic Corporation, Hauppauge, NY, USA). VR will be provided by VIVE Pro Eye, HTC (high-tech computer) Corporation, (New Taipei City, Taiwan) with digital rendering of forested greenspace. Once 1 h of SFIT concludes, the participant will be removed to the preparation area and given instructions related to reporting unanticipated problems, adverse events, and serious adverse events, and an appointment to return for follow up on Day 3. See Figure 1, which illustrates the SFIT process/procedure.

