##### P-Trak 8525, TSI, Shoreview, MN, USA

The P-Trak is a continuous ultrafine-particle (UFP) counter. The P-Trak has the capability of measuring particles as small as 100 nm. UFPs are currently studied to find associations with specific health effects [82]. The P-Trak will be zero-calibrated for each use using a charcoal filter. Both during the calibration and survey mode, research-grade isopropyl alcohol will be used in a small alcohol cartridge chamber in the instrument. The P-Trak has a data log that updates every minute and has a minimum and maximum range that is noted when the instrument is in survey mode. The data log will be downloaded onto a computer using software specific for the P-Trak [83]. All software will be accessed from the P-Trak website [81].

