##### Mini ppbRAE 3000, Honeywell International Inc., San Jose, CA, USA

The ppbRAE 3000 measures volatile organic compounds (VOCs) related to the phytoncides that we are atomizing. The ppbRAE 3000 will be zero-calibrated using a charcoal zero filter and Isobutylene Air Balanced span gas [84]. For two-point calibration, isobutylene at 10 ppm and 100 ppm will be used [85]. During two-point calibration, we will use a set 0.5 LPM regulator. This regulator can handle up to 500 psi, which is the psi of the span gas cylinders and also within the toleration limit of the ppbRAE 3000 regarding pressure and flow. It is important that the gas cylinder connection is CGA 600 and corresponds to the connection on the regulator, meaning that the threading has to be compatible between the cylinder and the regulator. If 500psi is exceeded during calibration or survey mode, the diaphragm within the RAE 3000 may be damaged, leading to inaccurate data collection. In survey mode, data will be updated every 60 s and a data log will be created. The data log will be downloaded using software specific to the ppbRAE 3000 and found online [82].

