##### Phytoncides, Floraplex Terpenes, Ypsilanti, MI, USA

α-pinene, β-pinene, and d-limonene are the phytoncides (forest oils) of interest for SFIT. Interestingly, all three in combination have been tested in normal males in both forest immersion and hotel/sleep contexts and have shown effective elevations in NK cell numbers and activity as well as increased expression of perforin and granulysin [5,6,20,21]. However, these three phytoncides have not been tested in the SFIT context with breast and prostate cancer patients. D-limonene alone has been tested in the context of pain and shown to be effective in an animal model when not paired with VR [88]. All three phytoncides are available as purified isolates in containers of 4, 8, or 32 ounces. The phytoncides will be added to the Asakuki atomizer with an easy calculation of ounces to ml, and that amount will be subtracted from the 500 mL total container in the atomizer so as to maintain a standardized addition of phytoncides:water ratio. Measurement of this mixed mist by ultrafine particulate and VOC survey will be the method of determining the dose of the phytoncide.

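### The protocol contradicts itself on what the VOC monitor measures, and a particle count that mainly follows water mist is part of the phytoncide dose and the drop-off test

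*Protocol article*

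**What the plan says.** Section 2.4 of the protocol article measures ambient phytoncide indirectly at the start and end of the 1 h session, from the rise in airborne particles and from the change in total VOCs. It assigns particle numbers to the P-Trak and states that "the total VOCs will be measured with the portable handheld monitor", meaning the Mini ppbRAE 3000. The next sentence says that these two instruments "will measure the increase in particle numbers and water droplets (aerosol), respectively, which will serve as a surrogate of relative exposure to phytoncide". The equipment section on the ppbRAE sides with the earlier sentence: "The ppbRAE 3000 measures volatile organic compounds (VOCs) related to the phytoncides".

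The readings have two stated uses:
- **Reaching the target.** Under section 2.4 the participant enters the room once a concentration of 0.80 ppm is reached. The equipment section on the phytoncides sets the dose method: "Measurement of this mixed mist by ultrafine particulate and VOC survey will be the method of determining the dose of the phytoncide".
- **Drop-off.** The feasibility part of section 2.5 takes P-Trak and ppbRAE readings before and after the hour and analyses drop-off by t-test at α = 0.05.

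On controls, section 2.2 says "They will be exposed to atomized water dispersal for 1 h", and that the same data are collected on them.

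**The concern.** A dose surrogate should move when the phytoncide moves and stay still when only the water does. Particle and droplet counts need not behave that way, because the atomizer disperses a mixture that is mostly water. The sections on room conditions and on the atomizer themselves warn that temperature and humidity affect particle and droplet readings and can condense the mist.

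Two results depend on the measure. One is the moment of entry, which is defined by a concentration. The other is the drop-off test, which is meant to show how stable the exposure is over the hour. If the particle count contributes to either, mist output can be read as phytoncide. A standardized way of delivering and measuring the exposure is the article's stated product, so the definition of the exposure measure is central to it.

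The sentence that calls the ppbRAE a droplet instrument adds to the problem. Read literally, it takes the only phytoncide-related channel out of the surrogate.

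**Working it through.** The document states no figure for this point, so there is none to reproduce. The check is a proportion and a comparison of sections.

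**1. Composition of the fill.** Inputs from the atomizer section: 500 mL capacity, 30 mL expected per phytoncide, and phytoncide volume replacing water. Number of phytoncides from section 3.1: three in study #1, one (d-limonene) in study #2.

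Water fraction = (500 − 30 × number of phytoncides) / 500.

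| | Phytoncide | Water | Water : phytoncide |
|---|---|---|---|
| Study #1 | 90 mL (18%) | 410/500 = 82% | 410/90 ≈ 4.6 : 1 |
| Study #2 | 30 mL (6%) | 470/500 = 94% | 470/30 ≈ 15.7 : 1 |
| Controls | 0 | 100% | – |

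**2. What this means for the count.** As an illustration, assume that the emitted mist has the composition of the fill and that the count is proportional to mist volume. If all phytoncide vanished from the mist and the water continued unchanged, the count would fall by only 18% in study #1 and 6% in study #2. If half the phytoncide were lost, it would fall by 9% and 3%. The atomizer is set to run for the full 60 min, so the count can hold steady while phytoncide falls. It can also change with humidity while phytoncide holds.

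**3. Units.** The target is a concentration in ppm. A particle count is not a concentration of phytoncide, and the article gives no rule for turning one into the other. The VOC monitor does read in ppm, but it is calibrated to isobutylene, so its reading and the target must be put in the same units before they are compared.

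**4. The sections side by side.**

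| Place | What the ppbRAE is said to measure |
|---|---|
| Section 2.4, sentence naming the instruments | Total VOCs |
| Section 2.4, next sentence | Water droplets |
| Equipment section on the ppbRAE | VOCs related to the phytoncides |
| Phytoncides section | A VOC survey contributes to dose (instrument not named) |

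The second row conflicts with the first and third. The conflict reaches the baseline too. The pre-session background in section 2.4 and the list of ambient conditions in the room-conditions section name particles and droplets, not VOCs. If droplets is shorthand for the ppbRAE reading, a VOC background is taken. If it is meant literally, none is stated.

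**The case against.** The strongest reply is that section 2.4 defines exposure by two measures, and that the second, total VOC, is related to the phytoncides. The abstract also links droplet measurement to VOCs, so the disputed sentence may be loose terminology for the ppbRAE reading. This reply stands as far as it goes: the VOC channel is in the plan and is suitable. It does not settle the contradiction. Nor does it remove the particle count from the dose definition or the t-test, or say which reading decides that the target has been reached.

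Four stronger readings are tempting and are not supported:
- **The exposure measure cannot tell the arms apart.** Water mist has no stated phytoncide content, so total VOC can separate phytoncide mist from water mist. The article also plans no between-arm comparison of exposure.
- **Alcohol from the P-Trak contaminates the VOC reading.** The article says "research-grade isopropyl alcohol will be used in a small alcohol cartridge chamber in the instrument". Nothing in it shows that a measurable amount escapes, and a steady background would cancel in a change score.
- **A span gas closer to the target is needed.** It is true that "isobutylene at 10 ppm and 100 ppm will be used", and 10/0.80 = 12.5. But the monitor is also zero-calibrated, so 0.80 ppm lies between the calibrated points 0 and 10 ppm.
- **The delivered dose is known to be wrong by a given factor.** The article gives no response factor, so any such figure would rest on an assumption. The conversion may also sit in the full protocol or a laboratory procedure that is not shown.

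The composition argument also has a limit: the figures describe the fill, and the article does not state the composition of the emitted mist.

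**Conclusion.** The concern holds for the particle and droplet part of the surrogate. Section 2.4 contradicts itself and the ppbRAE equipment section on what that instrument reads. The P-Trak count enters the dose measure and the drop-off test although the fill is 82% water in study #1 and 94% in study #2. Assuming that the emitted mist matches the fill, the count mainly reflects mist output and humidity, rises with water-only mist too, and cannot show that a ppm target is met or that phytoncide declines. The 18% and 6% bounds on its response further assume that the count is proportional to mist volume. They illustrate how weak the signal is and are not a measured error. The VOC measurement already in the plan is sound in principle, so the exposure assessment as a whole does not fail. It needs to be defined by that channel alone.

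**What to change.** 1. Correct the sentence in section 2.4 so that the P-Trak reads particle numbers and the ppbRAE reads total VOCs. Name VOC in the pre-session background and in the list of ambient conditions.
2. Make the VOC change the only measure for deciding that the stated target is reached and for the drop-off t-test. State that the isobutylene reading is converted to phytoncide, so that reading and target share one unit. The target itself is not at issue here.
3. Reference the VOC change to the pre-session reading and to the readings from the water-only control sessions. The pre-session reading also shows whether the room has cleared, which a control session needs if it is to serve as a reference.
4. Keep P-Trak counts as a check on mist output, and amend the dose sentence in the phytoncides section and the drop-off description in section 2.5 to match.

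The cost is minor rewording, a unit conversion and a background subtraction from data already planned. The particle count is lost as a dose measure. No instrument or participant is added.
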